#### Medication Adherence via the Medication Adherence Report Scale

The Medication Adherence Report Scale (MARS-5; [name]) [60] is a validated measure of medication adherence, with a Cronbach α of 0.67 [60,61]. It is the shorter version of the MARS-10. MARS-5 contains 5 items, each rated from 1 (always) to 5 (never). Total scores range from 5 to 25. In addition, participants are asked specifics about their OAA regimen such as timing, dose delays, interruptions, and stoppages [62].

#### Symptom Distress

Physical and psychosocial distress is measured using the Edmonton Symptom Assessment Scale Revised (ESAS-r). The current version, ESAS-r, has been revised to include psychosocial needs; depression, anxiety, and well-being [63,64]. Each item is rated from 0 (none) to 10 (worst possible). The scale has been tested in cancer populations (Cronbach **α**= 0.71).

### Data Analysis

Statistical analyses to be performed rely on Microsoft Excel, SPSS (version 25; IBM Corp) [65], and R (R Project for Statistical Computing) software [66]. For PDC, independent sample 1-tailed *t* tests will be performed to calculate the difference between 2 independent means of the experimental and control groups at one time point—study completion. Changes over time in MARS-5, MASES, and ESAS-r will be assessed using repeated-measures ANOVA. Between-group analyses will be conducted to examine how each group changed over time, and within-group analyses will be conducted to examine how participants changed over time.

The relationship between objective (PDC) and subjective (MARS-5) measures of medication adherence will be assessed using Spearman correlation coefficients. Oral chemotherapy knowledge at baseline and study exit will be compared using paired sample 1-tailed *t* tests.

Interviews were conducted individually, audio recorded, and transcribed verbatim by the first author, a doctoral candidate at the time with experience in qualitative research in oncology working on her dissertation. A reflexive journal was kept to document thoughts and feelings to recognize, acknowledge, and mitigate the influence of her role as a researcher and as someone with lived experience as an informal caretaker for a parent. Interview data were analyzed by the same author using thematic analysis as described by Braun and Clarke [67,68], beginning with several thorough readings of participant verbatim content to familiarize the researcher with the data and the identification of significant statements relating to the phenomenon under investigation [69]. Next, significant statements were placed into initial categories and organized into broader themes and subthemes. Themes and subthemes were reviewed, redefined, renamed, and explored as needed until no new themes emerged from the data.

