**Methods:**

A 2-arm, mixed methods, pilot randomized controlled trial took place at a large university-affiliated cancer center in Montreal, Quebec, Canada. Participants (N=52) completed baseline self-report e-questionnaires and subsequently were randomly assigned to the experimental group (intervention plus usual care, n=26) or control group (usual care only, n=26). The study intervention, designed to increase medication adherence via medication adherence self-efficacy and decreased symptom distress, included (1) OAA informational videos, (2) OAA-related e-handouts and other supportive resources, (3) nurse-led follow-up calls, and (4) e-reminders to take OAAs. The e-questionnaires were completed once a week for the first month and every 2 weeks for the subsequent 4 months, or until OAA treatment was completed. A subset from both groups (n=20) participated in semistructured interviews once they completed the study requirements. Study feasibility is assessed using recruitment, retention, and response rates, as well as intervention uptake. Through e-questionnaires and exit interviews, intervention acceptability is to be assessed prospectively at baseline and retrospectively upon study completion. Potential effects are then assessed via medication adherence self-efficacy, medication adherence self-report, and symptom distress.

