As OAA development and use expands, medication adherence issues related to OAAs are increasingly of interest to multiple stakeholders, including policy makers, insurance companies, drug makers, health care providers, and researchers [25]. A systematic review of factors influencing adherence to oral anticancer drugs identified three potentially modifiable factors that interventions should address: (1) side effects and toxicities, (2) forgetfulness, and (3) the lack of timely information [26]. The American Society of Clinical Oncology and the Oncology Nursing Society jointly released evidence-based guidelines and OAA management standards. These emphasize patient education at OAA initiation and ongoing monitoring throughout treatment to enable early identification of side effects and toxicities, thus preventing complications [27,28]. Consequently, there is a need for more timely and more accessible patient support for individuals taking OAAs [28].

A comprehensive, personalized, digital OAA intervention was developed based on Bandura’s [29] “Self-Efficacy Theory.” One of the intervention goals is to increase medication adherence by increasing medication adherence self-efficacy (SE) and symptom distress. SE refers to individuals’ beliefs in their own ability to successfully perform a specific task related to specific behavior, for instance, remembering to take medication on time to adhere to treatment, or effectively self-managing fatigue experienced from treatment [29,30]. A systematic review of the relationship between SE and medication adherence found a positive link between these two variables in 59 out of the 66 studies reviewed [31]. Behavior is influenced by the interaction between perceived SE and expectations surrounding the outcome of the behavior; thus, medication adherence is affected by a patient’s belief in their capacity to consistently remember to take medication and the belief that consistently taking the medication, as prescribed, will be an effective treatment to kill cancer cells in their body. Knowledge and self-management skills of disease care can enhance SE through expectations [32]. In support of this, a standardized patient education and follow-up intervention for oral chemotherapy by Tokdemir and Kav [33] successfully increased medication adherence SE after the intervention (66.39 vs 71.04; *P*<.05). Herein, we tested a broader multimodal intervention that went beyond patient education.

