**Preliminary effects of the intervention**											
	Medication adherence	Proportion of days covered		Chart review		—		—	—	—	✓
	Medication adherence	Medication Adherence Rating Scale ([name])		5		—		✓	✓	—	—
	Medication adherence self-efficacy	Medication Adherence Self-Efficacy Scale		20		✓		✓	✓	—	—
	Symptom distress	Edmonton Assessment Scale revised		12		✓		✓	✓	—	—

^a^Not applicable.

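### PDC is to be compared by an unadjusted t test, although baseline MASES, completed before randomisation, could be used as a covariate for a small gain in precision

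*Protocol article*

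**What the plan says.** The Data Analysis section introduces the PDC comparison with "For PDC, independent sample 1-tailed" t tests. These "will be performed to calculate the difference between 2 independent means of the experimental and control groups at one time point", namely study completion. A two-sample t test has no place for a covariate, so for PDC the article fixes an unadjusted analysis. For the other effect outcomes it says: "Changes over time in MARS-5, MASES, and ESAS-r will be assessed using repeated-measures ANOVA".

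Table 1 lists PDC as a chart review at study completion, with nothing at baseline. The same table ticks the 20-item "Medication Adherence Self-Efficacy Scale" at baseline. The abstract says that participants "completed baseline self-report e-questionnaires and subsequently were randomly assigned to the experimental group" or control. The section on recruitment, consent and randomisation gives the same order.

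On the link between the two measures, the abstract describes the intervention as "designed to increase medication adherence via medication adherence self-efficacy and decreased symptom distress". The Background cites a systematic review of self-efficacy and medication adherence that "found a positive link between these two variables in 59 out of the 66 studies reviewed". No correlation coefficient is given.

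The Results section reports a final sample of 41: 23 experimental and 18 control.

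**The concern.** A baseline variable that predicts the outcome, measured before allocation, can be put in the analysis model to remove explained variance from the error term. Baseline MASES meets the timing condition. By the article's own reasoning it is also a plausible predictor of adherence. PDC has no pre-randomisation value, so adjustment for its own baseline is not available and another baseline measure is the only route.

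With 41 participants the confidence interval for the PDC difference will be wide, and a future trial may be planned from it. If baseline MASES correlates well with PDC, the t test gives away precision that costs nothing to collect.

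**Working it through.** **The plan's own figure.** The Sample Size section gives 36 before attrition and 52 after. Attrition checks: 36/(1 - 0.30) = 51.4, rounded up to 52. The 36 is reproduced for a within-between interaction in a repeated-measures ANOVA (f = 0.25, alpha 0.01, power 0.95) if one assumes 6 measurements, correlation 0.5 and no sphericity correction (power 0.951). That calculation is for a different test. It gives no power for PDC and is unaffected by this point.

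**Inputs for PDC**
- From the documents: n = 23 and 18 (Results); 1-tailed t test (Data Analysis).
- Assumed: all 41 have a PDC value; one-sided level 0.05, as no level is stated for this test; true difference 0.5 or 0.8 SD; within-arm correlation r between baseline MASES and PDC from 0.1 to 0.5.

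**Formulas**
- Standard error of the raw difference, in SD units: sqrt(1/23 + 1/18) = 0.315.
- Unadjusted: noncentral t, df = 23 + 18 - 2 = 39, noncentrality d/0.315. This is about 1.59 at d = 0.5 and 2.54 at d = 0.8.
- ANCOVA: residual variance multiplied by (1 - r²), so noncentrality is d/(0.315 × sqrt(1 - r²)), with df = 38.
- Equivalent unadjusted sample: 41/(1 - r²).

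| r | 1 - r² | 41 is worth | Power, 0.5 SD | Power, 0.8 SD |
|---|---|---|---|---|
| t test | 1 | 41 | 46.7% | 80.3% |
| 0.1 | 0.99 | 41.4 | 47.0% | 80.6% |
| 0.2 | 0.96 | 42.7 | 47.9% | 81.7% |
| 0.3 | 0.91 | 45.1 | 49.6% | 83.4% |
| 0.4 | 0.84 | 48.8 | 52.3% | 86.0% |
| 0.5 | 0.75 | 54.7 | 56.2% | 89.2% |

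The smallest difference detectable with 80% power is 0.80 SD unadjusted, 0.76 SD at r = 0.3 and 0.69 SD at r = 0.5.

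**If the level were one-sided 0.01** (the alpha in the Sample Size section), power at 0.8 SD goes from 55.1% to 59.6% at r = 0.3 and 69.3% at r = 0.5.

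**A qualification at the low end.** The table ignores the small variance cost of estimating the MASES slope when the arms differ by chance on MASES. That cost multiplies the variance by about (41 - 3)/(41 - 4) = 38/37. The net factor is 0.99 × 38/37 = 1.017 at r = 0.1 and 0.75 × 38/37 = 0.770 at r = 0.5. Adjustment therefore pays only if r² exceeds 1/38, that is, r above about 0.16.

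**Chance imbalance.** The difference in mean baseline MASES between arms of 23 and 18 has a standard error of 0.315 SD. At r = 0.4, an imbalance of that size moves the raw PDC difference by 0.4 × 0.315 = 0.126 SD. This is a component of the t test's standard error and not an addition to it: 0.126² = 0.016, which is r² = 0.16 of the total variance 0.315² = 0.099.

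**The case against.** The strongest reply is that the article states nothing wrongly here. The t test is a standard and valid choice, its standard error already covers chance imbalance, and the theory says that raising self-efficacy raises adherence, not that a baseline score predicts later pharmacy fills. The cited review is summarised only as a count of studies, and some participants answer MASES before taking any drug. All of this stands. It limits the point to precision and leaves the size of the gain open. It does not remove the point, because the article commits to a test that cannot use a covariate already in hand.

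A reader might infer four stronger things that the documents do not support.

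- **That MARS-5 has the same fault.** For MARS-5 the article names repeated-measures ANOVA and is silent on covariates, a detail that an article may leave to the analysis plan. Moreover, the test behind the sample size is the group-by-time interaction. With complete data, a baseline covariate entered as a main effect leaves that interaction's error term unchanged.
- **That MASES is the only prognostic baseline measure.** Symptom distress is the other pathway named in the abstract, and ESAS-r is also ticked at baseline in Table 1. MASES is one defensible choice.
- **That chance imbalance biases the PDC result.** It does not, as shown in the working.
- **That unequal losses make the raw comparison biased.** If 26 per arm were randomised, losses were 3 and 8. That split is compatible with chance (Fisher p = 0.17), and nothing in the article ties dropout to self-efficacy.

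**Conclusion.** The point holds for PDC alone, as a minor one. The unadjusted 1-tailed t test is valid but may be less precise than an analysis using baseline MASES. Under the stated assumptions the power gain runs from 0.3 to 9.5 percentage points at 0.5 SD and from 0.3 to 8.9 points at 0.8 SD. It is about 3 points at r = 0.3 and effectively nothing below r of about 0.16. The result rests on an unknown correlation, a one-sided 0.05 level, PDC being available for all 41, and normal-theory power for a bounded outcome. Feasibility and acceptability are the primary outcomes of this pilot and intervention effects are exploratory, so no main conclusion depends on it.

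**What to change.** Before arm comparisons are run, declare as a change to the published plan that PDC will be compared by ANCOVA with arm and baseline MASES. Use only the baseline MASES value, because later values are measured after allocation and lie on the presumed causal path. Report the adjusted arm difference with a 95% CI, and keep the unadjusted t test as a sensitivity analysis. If the arms have already been compared, label the adjusted result post hoc.

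The cost is one degree of freedom (39 to 38) and no new data. If the correlation is near zero, the two analyses will nearly agree and little is lost. The model also estimates the association between baseline MASES and PDC, which a larger trial could use in planning.

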**Figure 1 figure1:**
[figure not shown]
Study aims, objectives, and measures.

The second aim is to determine the acceptability of the intervention. The definition and measures of acceptability are based upon theoretical framework of acceptability of health care interventions by Sekhon et al [35], which defines acceptability as a multifaceted construct reflecting the appropriateness of the intervention. A key feature of this framework is the distinction between prospective, concurrent, and retrospective acceptability, emphasizing that acceptability can be assessed before, during, and after the intervention as all 3 can have an impact on participant use and access to the intervention. Although Sekhon et al [35] propose 7 concepts of intervention acceptability, only the 3 most relevant are included herein, namely intervention burden, coherence, and perceived effectiveness.

The third aim of the study focuses on documenting the potential effects of the intervention: As stated in the CONSORT (Consolidated Standards of Reporting Trials) on randomized pilot and feasibility trials [36], pilot trials may assess potential effectiveness using surrogate outcomes—substitute measures used as alternatives to clinical outcomes that may be challenging to assess directly [36]. Herein, potential intervention effects are assessed by comparing experimental and control groups over time, from baseline, every 2 weeks (depending on the outcome), and after the intervention. It is hypothesized that over time, compared to the control group, the experimental group will report higher medication adherence SE, higher medication adherence, and lower overall symptom distress.

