#### Sample Size

Sample size calculation was undertaken using procedures provided by the software program G*Power 3 [37]. As per our statistical consultant, the calculation was undertaken to determine adequate power in the determination of the potential effects of the intervention (aim 3), in which a repeated-measures ANOVA with a within-between interaction would be the statistical test used. The parameters for the power calculation included an effect size of 0.25 (standard medium effect size for ANOVA) [38], α of .01, and a power of 0.95. The sample size was further increased to account for a 30% attrition rate over the study duration, determined to be appropriate given a review of attrition rates in supportive oncology trials found a mean of 26% (95% CI 23%-28%) across 18 trials (ie, the original sample size was 36, total with added 30%, attrition is 52) [39].

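### MASES and ESAS-r: the repeated-measures ANOVA most naturally carries the pre-randomisation score as an outcome occasion; using it as a covariate would give aim 3 a sharper, directional estimate

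*Protocol article*

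**What the plan says.** Data Analysis names the model: "Changes over time in MARS-5, MASES, and ESAS-r will be assessed using repeated-measures ANOVA". It describes the comparison of arms as follows: "Between-group analyses will be conducted to examine how each group changed over time". No covariate is mentioned.

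Sample Size names the aim 3 test: "a repeated-measures ANOVA with a within-between interaction would be the statistical test used".

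Purpose of Study sets the time frame, which runs until the intervention has ended: "potential intervention effects are assessed by comparing experimental and control groups over time, from baseline, every 2 weeks (depending on the outcome), and after the". The hypothesis there is directional: over time, the experimental arm should have higher self-efficacy, higher adherence and lower symptom distress than control.

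Table 1 ticks baseline for the "Medication Adherence Self-Efficacy Scale" (MASES) and for the ESAS-r, but not for MARS-5. The Abstract puts the baseline questionnaires before random assignment. The point therefore concerns MASES and ESAS-r only.

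**The concern.** A score taken before randomisation cannot have been changed by the intervention. Its best use is to explain variation between people in the later scores. In a repeated-measures ANOVA that starts at baseline it is instead part of the outcome, and the model offers two terms bearing on the arms.

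- **Group-by-time interaction.** This asks whether the two profiles differ in shape in any way. It is non-directional. A benefit that appears early and persists is one contrast, baseline against the rest, among all the degrees of freedom tested. A significant F gives no single effect size to carry forward.
- **Group main effect.** This averages over all occasions, baseline included, so the benefit is diluted and any chance baseline difference stays in the estimate.

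At stake is how much a small pilot can learn about potential effects from data it already holds, and whether it passes a usable estimate with a confidence interval to the next trial.

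**Working it through.** **1. The plan's own figure.** Sample Size gives "an effect size of 0.25 (standard medium effect size for ANOVA"), "α of .01, and a power of 0.95" and "the original sample size was 36, total with added 30%, attrition is 52". The article does not give the number of measurements, the correlation or the sphericity factor. With 6 measurements, correlation 0.5 and no sphericity correction (assumed), the usual within-between formula is λ = f²·N·m/(1−ρ) = 0.0625 × 36 × 6 / 0.5 = 27 on 5 and 170 df. Power at .01 is 0.951 for N = 36, and 36/0.70 = 51.4, rounded up to 52. Both figures reproduce under those assumptions.

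**2. Inputs for the comparison.**
- From the article: 23 and 18 analysed (Results). One month of weekly and four months of two-weekly questionnaires (Data Collection) give about 4 + 8 = 12 follow-ups, or 13 occasions with baseline. f = 0.25 equals d = 0.5 for two groups.
- Assumed: a benefit of d = 0.5 SD constant over follow-up; complete data; correlation ρ equal between all occasions; k = 5 or 12 follow-ups, with m = k + 1; two-sided .05.

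The SE of a difference in means, in SD units, is √(1/23 + 1/18) = 0.315. This is also the SD of a chance baseline difference.

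**3. Formulas, with k = 12 and ρ = 0.5.**
- Main effect including baseline: effect d·k/m = 0.5 × 12/13 = 0.462; variance (1 + kρ)/m = 7/13 = 0.538; noncentrality 0.462/(√0.538 × 0.315) = 2.00; power 0.496.
- Follow-up mean, unadjusted: variance (1 + (k−1)ρ)/k = 6.5/12 = 0.542; noncentrality 0.5/(√0.542 × 0.315) = 2.16; power 0.558.
- Follow-up mean, baseline-adjusted: variance 0.542 − ρ² = 0.292; noncentrality 0.5/(√0.292 × 0.315) = 2.94; power 0.818. This ignores the small cost of estimating the slope.
- Interaction: λ = d²·(k/m)/[(1/23 + 1/18)(1−ρ)] = 0.25 × 0.923 × 10.10/0.5 = 4.66 on 12 and 468 df; power 0.224. The same λ on a single degree of freedom (t noncentrality √4.66 = 2.16) would give 0.558, which shows the price of spreading it.

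| k | ρ | Main effect incl. baseline | Follow-up mean, unadjusted | Follow-up mean, adjusted | Interaction | Adjusted minus main (points) |
|---|---|---|---|---|---|---|
| 5 | 0.3 | 0.516 | 0.647 | 0.744 | 0.217 | 23 |
| 5 | 0.5 | 0.394 | 0.516 | 0.744 | 0.298 | 35 |
| 5 | 0.7 | 0.320 | 0.428 | 0.846 | 0.488 | 53 |
| 12 | 0.3 | 0.672 | 0.735 | 0.848 | 0.164 | 18 |
| 12 | 0.5 | 0.496 | 0.558 | 0.818 | 0.224 | 32 |
| 12 | 0.7 | 0.391 | 0.444 | 0.891 | 0.380 | 50 |

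**4. Where the main-effect gap comes from.** At ρ = 0.5, removing baseline from the average recovers 6 points with 12 follow-ups (0.496 to 0.558) and 12 points with 5 (0.394 to 0.516). The remaining 26 and 23 points come from adjusting for baseline. Non-adjustment is the larger part.

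**5. Other covariance shapes.** Simulation, 13 occasions, same effect, 2,000 trials per row, Greenhouse-Geisser correction for the interaction:

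| Covariance (assumed) | Main effect | Interaction | Adjusted mean |
|---|---|---|---|
| Equal correlation 0.3 | 0.68 | 0.13 | 0.84 |
| Equal correlation 0.5 | 0.50 | 0.18 | 0.82 |
| Equal correlation 0.7 | 0.39 | 0.30 | 0.88 |
| Autoregressive 0.90 per week | 0.50 | 0.08 | 0.76 |
| Autoregressive 0.95 per week | 0.39 | 0.12 | 0.81 |

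A second simulation covering both 6 and 13 occasions gave 0.28-0.65, 0.11-0.46 and 0.61-0.90 respectively.

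**6. Sensitivity.**
- At the planned α of .01 (d = 0.5, 5 follow-ups), main effect against adjusted mean is 0.27 v 0.50, 0.18 v 0.50 and 0.13 v 0.64 for ρ = 0.3, 0.5 and 0.7.
- At d = 0.8, α .05 and 12 follow-ups, the main-effect loss is only 3, 12 and 23 points for the same ρ.
- If the benefit grows linearly to 0.8 SD, the interaction has 0.38-0.95 and the adjusted mean 0.51-0.82, so either can win.

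**7. Why the planned 0.95 does not contradict this.** In the sample-size formula f measures how much the interaction varies over all occasions. A sustained 0.5 SD shift with 5 follow-ups and ρ = 0.5 gives λ = 0.25 × 0.833 × 10.10/0.5 = 4.2 at 23 v 18, not 27.

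**The case against.** The strongest reply is that the article does name its test. Sample Size specifies the within-between interaction, and Data Analysis frames the between-group analysis as change over time. For that test a baseline occasion belongs in the model, and a baseline difference that simply carries forward does not appear as an effect. This stands. A reader might infer that the plan tests a wrong null, or that chance imbalance biases its main test. The documents do not support that: dilution and imbalance apply only to a group main effect, and nothing says that the hypothesis is judged on one.

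A reader might also quote a single figure for lost power, or blame it on averaging in baseline. Neither is supported. The article gives no correlation, effect shape or number of analysed occasions. Even the 13 occasions are uncertain: the CAD $120 ceiling at CAD $10 per set implies 12 sets including baseline, and follow-up stops when treatment ends. Most of the main-effect loss comes from non-adjustment.

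Third, this is a condensed article, and a full analysis plan may already specify a covariate. That is possible. The point rests on the model that the article does name, which as described makes baseline an outcome.

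Finally, Data Collection calls feasibility and acceptability the primary outcomes, so no decision hangs on an aim 3 p-value. That limits the consequence, but does not remove the value of a better estimate at almost no cost.

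**Conclusion.** The point holds as an efficiency and clarity improvement. For a sustained 0.5 SD benefit with 23 v 18 complete cases and two-sided .05, the baseline-adjusted follow-up mean has power of about 0.6-0.9. The interaction has about 0.1-0.45 after Greenhouse-Geisser correction, and a main effect including baseline about 0.3-0.7. The gain over the main effect is roughly 15-55 points for correlations of 0.3-0.7, and smaller for larger effects. With a growing benefit the ranking against the interaction can reverse. All these figures rest on assumed correlations, effect shape, number of occasions and complete data. The planned interaction test is not invalid, MARS-5 is unaffected, and aim 3 is secondary in this pilot.

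**What to change.** For MASES and ESAS-r:

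- Take baseline out of the outcome vector. Fit a repeated-measures model to the follow-up occasions with arm, time, arm-by-time and the baseline score as a covariate.
- Name the baseline-adjusted arm difference averaged over follow-up, with its confidence interval, as the aim 3 estimate.
- Report the arm-by-time term alongside it.
- State that no group main effect from a model with baseline as an occasion will be interpreted.

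The cost is a change of analysis wording, because the baseline scores are already collected. The article says that results are still to be published; if the analysis has already been run, label the adjusted estimate as added after the plan. The drawback is that an average over follow-up is less sensitive to a late or growing benefit, which is why the arm-by-time term stays in the report.
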